### Secondary outcome measures

#### Body mass index

Weight will be measured using calibrated scales (SECA 708, Hamburg, Germany), weighing to the nearest 0.01 kg. Height will be determined using a standard calibrated stadiometer (Holtain Limited, Crymych, Pembrokeshire, UK) measured to the nearest 0.01 metres with the participant standing in the anatomical position. BMI will be calculated using the following formula: weight (kg)/height (m^2^). Three measurements will be taken and the mean of the two closest measurements used.

### Waist circumference

Waist circumference will be measured using a steel tape measure with the participant in the standing position. The tape will be placed horizontally around the participant’s waist immediately above the iliac crest according to the NHANES III procedure [83]. Three measurements will be taken and the mean of the two closest measurements will be used.

### Hip circumference

Hip circumference will be measured using a steel tape measure with the participant in the standing position. The tape will be placed horizontally around the widest part of the hips [84]. Three measurements will be taken, and the mean of the two closest measurements used.

### Sit to Stand test in 30 seconds

The Sit to Stand test in 30 seconds (STS-30) as described previously [85] will be performed as a functional weight-bearing performance test for the lower body and a test for lower limb muscular endurance. The test commences following a demonstration of technique and cueing from the researcher and is practised by the participant for up to ten repetitions with feedback on technique. The participant then rests for up to 3 minutes or until fully recovered before commencing the 30-second test. The test commences in the seated position and the participants are instructed to hold their arms across their chest for the test duration. The participant will be required to sit back on the chair but not collapse back into the chair prior to the next repetition. If the participant is more than half way up at the end of 30 seconds then the repetition will be rounded up. The chair will be set at the height of the popliteal crease and recorded to replicate in later tests.

### Objective assessment of physical activity and sedentary behaviour

Participants will be fitted with an Acti-heart® heart rate and activity monitor that will be worn for 7 days as described previously [86, 87]. The monitor is attached by two standard electrodes on the chest, placed immediately lateral to the sternum at the second intercostal space with the second electrode attached on the same horizontal level as far lateral as possible. The area is cleaned with a 73 % ethanol swab prior to electrode placement. The device will be worn for seven consecutive days without being removed (unless electrodes require replacing) and data will be analysed to determine the duration of sedentary behaviour (<1.5 METS), light intensity (1.5–2.9 METS), and moderately intense activity (≥3 METS) [88] in bouts of at least 1 minute and at least 10 minutes. Participants will be blinded to the device’s ability to record activity data.

### Subjective assessment of physical activity behaviour

Participants will complete the Baecke physical activity questionnaire as a measure of habitual physical activity over the previous 12 months [89]. Separate work, sport and leisure index scores will be calculated, plus a total score.

### Seven-day exercise recall

Participants will be interviewed during consultations prior to the commencement of the physical tests. The participant will be guided through a recall of the previous 7 days for engagement in exercise bouts of at least 10 minutes in duration. Intensity will be reported by the participant through description of effort, breathing or the use of the Borg scale for ratings of perceived exertion [90]. The weekly time spent exercising at moderate to vigorous intensity for bouts of at least 10 minutes will be used for analysis. This lower limit was set due to a lack of health benefits achieved at lower duration and intensities [91].

### Blood sampling and analysis

#### Fasting blood collection and analysis

Venous blood samples will be collected prior to the oral glucose tolerance test (OGTT) by a trained phlebotomist. Forty millilitres of blood will be extracted into vacutainer tubes, and two tubes will be sent to a commercial pathology laboratory for analysis of fasting glucose, insulin, blood lipids, haemoglobin A1c, and C-reactive protein. The remaining blood will be centrifuged and stored in a freezer at −80 °C. Markers of systemic inflammation and bone metabolism will be analysed as described previously [92, 93]. Each participant is advised to maintain their normal diet and exercise patterns for the 3 days prior to the testing. After a 12- hour overnight fast, participants will attend the Baker IDI Heart and Diabetes Institute. Baker IDI Heart and Diabetes Institute research colleagues will perform muscle sympathetic nerve activity recording, endothelial function assessment and the OGTT. An intravenous catheter will be placed in an antecubital vein for blood sampling. Volunteers will ingest 75 g of glucose over 2 minutes (Glucotol™, Orion Laboratories, Welshport, WA, Australia). Blood samples will be drawn at −15, 0, 30, 60, 90 and 120 minutes for determination of plasma glucose and insulin concentrations. The remaining blood will be centrifuged and plasma will be stored in a freezer at −80 °C at the Baker IDI Heart and Diabetes Institute. Markers of bone metabolism and systemic inflammation will be analysed as described previously [92] from the stored samples.

### Muscle sympathetic nerve activity (MSNA) recording

Recordings of multi-unit post-ganglionic MSNA will be made while the subject rests in a comfortable supine position. A tungsten microelectrode (FHC, Bowdoinham, ME, USA) will be inserted directly into the right peroneal nerve at the fibular head by an experienced investigator [name]. During MSNA recording, blood pressure (BP) will measured continuously using the Finometer system (Finapress Medical System BV, Amsterdam, The Netherlands) and heart rate (HR) will be extracted from a three-lead ECG. All of these parameters will be digitised with a sampling frequency of 1000 Hz (PowerLab recording system, model ML 785/8SP, ADInstruments, Bella Vista, NSW, Australia). Resting measurements will be recorded over a 15-minute period and averaged. Sympathetic bursts will be counted manually and expressed as burst frequency (bursts/minute) and burst incidence (bursts/100 heart beats).

### Twenty-four-hour ambulatory blood pressure monitoring

Participants will be fitted with ambulatory blood pressure monitoring equipment (Oscillometric monitor, model number 90207, SpaceLabs Medical Inc., WA, USA) before leaving the Baker IDI Heart and Diabetes Institute on the first day at each assessment timepoint. The device will be worn around the waist with a belt while the cuff will be fitted to the upper left arm to measure brachial blood pressure every 15 minutes between 6 am and 10 pm, and every 30 minutes between 10 pm and 6 am. Participants will be advised to record their activity and any symptoms at each reading. The monitor is removed after 24–26 hours of continuous wear and then returned via a self-addressed express post satchel or in person to the Baker IDI Heart and Diabetes Institute. Blood pressure values will be averaged over the total recording time for a 24-hour average, and separately across waking and sleeping hours [94]. Resting blood pressure will be also recorded in the clinic after sitting quietly for 5 minutes. Blood pressure will be taken by an experienced researcher using a standard aneroid sphygmomanometer, listening for the first and last Korotkoff sounds through the brachial artery with a stethoscope.

### Spontaneous cardiac baroreflex function

Baroreflex sensitivity will be assessed using the sequence method from analysis of the continuous (beat-to-beat) blood pressure and heart rate fluctuations. The procedure identifies the ‘spontaneous’ sequences of three or more consecutive beats in which systolic blood pressure progressively rise (by at least 1 mmHg) and cardiac interval lengthens, or systolic blood pressure progressively falls (by at least 1 mmHg) and cardiac interval progressively shortens, with a lag of one beat. For each sequence, the linear correlation coefficient between cardiac interval and systolic blood pressure will be computed and the sequence validated when *r* >0.80. The slope between cardiac interval and systolic blood pressure will be calculated for each validated sequence and an average slope will be calculated for each recording. These measures will be extend by including assessment of baroreceptor modulation of MSNA (or vasomotor tone) by relating each spontaneous sympathetic burst to the diastolic blood pressure and cardiac interval of the heart beat during which the burst is generated [95].

### Endothelial function

The Endo-PAT 2000 will be used to non-invasively assess endothelial function and arterial stiffness. The device captures a beat-to-beat plethysmographic recording of the finger arterial pulse wave amplitude with pneumatic probes, detecting the peripheral arterial tone. Peripheral arterial tonometry is assessed in response to reactive hyperemia by placing the finger probe on the index finger in each hand (occluded study hand, and non-occluded, control hand). Measurements will be obtained for 5 minutes at baseline followed by 5 minutes of occlusion of one arm, with cuff inflated on the upper arm to supra-systolic pressure and then released to induce reactive (flow-mediated) hyperaemia, measured for 5–10 minutes. The magnitude of flow-mediated hyperaemia is calculated as the ratio between post- obstructive and baseline pulse wave amplitude, corrected to systemic changes measure in the contralateral, non-obstructed arm. Arterial stiffness is assessed by automatic calculating the Augmentation Index from the pulse arterial tonometry waveform.

### Quality of life questionnaires

The Medical Outcomes Trust (MOT) SF-36 (short form 36) health-related quality of life questionnaire contains 36 questions regarding the multi-dimensions of health. Question categories include: limitations of activities, general health, physical health problems, emotional health problems, social activities, pain, and energy and emotions [96, 97]. The questionnaires will be printed and provided to participants to complete at each timepoint.

### Multi-dimensional Body-Self Relations Questionnaire

The Multi-dimensional Body-Self Relations Questionnaire is a validated questionnaire [98] and the Appearance Orientation (AO) and Appearance Evaluation (AE) subscales have previously been used in this patient population [99]. AO quantifies the importance placed on appearance and grooming, and is scored on five-point responses (definitely disagree to definitely agree) to 12 questions. The AE score is comprised of seven items (again with five-point responses) and describes the participant’s perception of their own attractiveness.

The Work Productivity and Activity Impairment Questionnaire (WPAI) is a short self-report instrument that requires the participant to recall their work practices over the past 7 days. It has been used previously to assess work productivity loss and the degree of impairment to activity due to obesity and obesity-related co-morbidities [100].

### Epworth Sleepiness Scale

The Epworth Sleepiness Scale assesses daytime sleepiness during various situations on a four- point scale from 0 (would never doze) to 3 (high chance of dozing) [101].

### Musculoskeletal Pain Questionnaire

Participants will complete an 11-point (0–10) Likert visual analogue scale (VAS) to report pain in nine regions around the body as described elsewhere [102].

### Self-efficacy questionnaires

The Exercise Self-efficacy Scale (ESE) measures perceived competence to overcome barriers to completing exercise. The five items on the scale require the participant to rate the statement from 1 (not at all confident) through to 7 (very confident). The second self-efficacy scale, the Weight Efficacy Lifestyle Scale (WEL), measures self-efficacy for appropriate eating. It has five subscales (negative emotions, availability, social pressure, physical discomfort, positive activities) with four items each. Each item presents a statement that is then ranked on a 10-point scale, 0 (not confident) to 9 (very confident) [103, 104].

### Beck Depression Inventory-II

The Beck Depression Inventory-II (BDI) [105] is a revision of the original 21-item questionnaire with scores ranging from 0 to 3 on a 4-point Likert-type scale for each question (responses ranging from ‘not at all’ to an extreme form of each symptom) used to assess severity of depressive symptoms over the past 2 weeks including the current day, in populations aged 13 years and over. This tool is not used for diagnostic purposes, rather it is used to identify and score the severity of symptoms of depression.

### Spielberger State and Trait Anxiety Inventory

The Spielberger State and Trait Anxiety Inventory (STAI) is used to measure the presence and severity of current symptoms of anxiety along with general tendency to be anxious via self-report [106]. This tool consists of two questionnaires of 20 items each, the first questionnaire is used to measure state anxiety (feelings of anxiety at the time of administration) while the second, measures trait anxiety (general feelings of anxiety) [107]. Each questionnaire uses a four-option response scale from ‘not at all’ to ‘very much so’ (scored from 1 to 4) in the state anxiety questionnaire and ‘almost never’ to ‘almost always’ (scored from 1 to 4) for trait anxiety [106]. Scores range from 20 to 80 for each questionnaire with higher scores indicate greater anxiety. A cut-point of 39 to 40 being set for clinically significant symptoms of state anxiety [108, 109].

### Statistical analysis

All variables will be plotted and visually inspected for skewness and kurtosis. Formal analysis of normality will be confirmed with the Kolmogorov-Smirnov test of normality (SPSS statistics for windows, version 21.0: IBM Corp., Armonk, NY, USA) as it is appropriate when used with small- to medium-sized samples [110]. The independent *t* test for continuous variables will be used to examine the groups (ER versus EXER) characteristics at baseline using Genstat statistical software (for Windows 16th edition. VSN International, Hemel Hempstead, UK). Genstat will be used to produce a histogram of residuals, fitted-value and normal plot of residuals and assessed for normality, independence, equal variance and linearity for each dependent variable. If the data is shown to not be normally distributed or displays heteroscedasticity the data will be log transformed to restore normality [111]. Factorial repeated measures analysis of variance (ANOVA) (mixed between-within subjects or split-plot) with intention-to-treat protocol for all variables to assess the interaction effect (group × time) will be performed. Missing values for variables will be replaced using an expectation maximisation algorithm with a multiple imputations method [112] using Genstat statistical software. Analysis for the least significant difference of the means will be performed for both time and group with a *p* value set at 0.05.

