**Methods/Design:**

Sixty women, aged 18–50 years with a body mass index (BMI) greater than 34.9 kg.m^2^ and at least one obesity-related co-morbidity, will be recruited for this 12-month study. Participants will be randomised to either exercise plus energy restriction (*n* = 30), or energy restriction alone (*n* = 30). All participants will follow an energy-restricted individualised diet incorporating a VLED component. The exercise intervention group will also receive exercise by supervised aerobic and resistance training and a home-based exercise programme totalling 300 minutes per week. Primary outcome measures include body composition and aerobic fitness. Secondary outcome measures include: physical function, cardiometabolic risk factors, quality of life, physical activity, and mental health. All outcome measures will be conducted at baseline, 3, 6 and 12 months.

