### Sample size

The number (*n* = 60) of participants to be recruited for this study has been determined based on previous evidence, plus a projected drop-out rate of 25 %, and provide adequate statistical power for the two co-primary outcome measures of VO_2peak_ (*n* = 20, *α* = 0.05, power 0.9 [74]) and lean mass (*n* = 23, SD of 1.7, *α* = 0.05, power 0.8 [75]). Secondary outcome measures for traditional markers of cardiometabolic health including systolic and diastolic blood pressure, total cholesterol, LDL cholesterol, insulin sensitivity; and measures of physical activity require fewer participants to reach statistical power (range *n* = 8–14, *α* = 0.05, power 0.8).

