### Randomisation

Participants will be randomised individually by a researcher external to the project and will have no contact with the participants prior to or during the trial. This researcher will have no intellectual or personal investment into the study design or outcomes. The women will be randomised into either (ER) or (EXER) groups using sealed opaque envelopes in blocks of six. The envelopes will be stored in a locked cabinet within the independent researcher’s office. Each envelope will contain a single sheet of paper identifying the group allocation. The sheet of paper will be folded at least twice to reduce chance of transparency. One envelope will be chosen at random from the stack of six envelopes containing three of each group allocation (EX and EXER) reduced to a single envelope; this is then combined with the next group of six envelopes to reduce the chance of predictability. The independent researcher is provided with a participant identification number and completes randomisation once the prospective participant provides the study investigators ([name]) with a medical clearance from their own general practitioner, preliminary participant screening, and completes all of the baseline measures to ensure safety and suitability for study participation. Participants, and researchers involved in delivering participant interventions will not be blinded to group allocation. Some of these researchers ([name]) will also be involved in study co-ordination and data collection.

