### Measures

Outcome measures will be obtained from participants at baseline, 3, 6, and 12 months. The series of tests at each location is shown in Fig. 1. Trained research staff will adhere to the standardised procedures for all data collection ensuring consistency in (1) order of tests, (2) use the same equipment for each test, and (3) management and storage of data collected.

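### Baseline is analysed as one of the four visits and not as a covariate: the interaction test is valid, but precision is lost for outcomes with a moderate baseline-to-follow-up correlation

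*Protocol article*

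**What the plan says.** The Statistical analysis section of the protocol article names one efficacy method for all variables: "Factorial repeated measures analysis of variance (ANOVA) (mixed between-within subjects or split-plot) with intention-to-treat protocol for all variables to assess the interaction effect" of group by time. According to the Measures section, "Outcome measures will be obtained from participants at baseline, 3, 6, and 12 months". The article sets none of these visits apart from the time factor. It does not say in words that baseline is a level of time, but with four visits and a group-by-time target that is the natural reading.

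Apart from this, baseline appears in the analysis only in an independent t test that "for continuous variables will be used to examine the groups (ER versus EXER) characteristics at baseline". No covariate adjustment is mentioned anywhere. After the ANOVA, "Analysis for the least significant difference of the means will be performed for both time and group", with the p "value set at 0.05". The Randomisation section allocates women to "groups using sealed opaque envelopes in blocks of six" and states no stratification by a baseline value.

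**The concern.** In a randomised trial the baseline value is measured before allocation, so treatment cannot affect it. Used as a covariate, it removes the part of the follow-up variance that it predicts. Used as another response level, it enters each follow-up-versus-baseline contrast with a fixed weight of −1, whatever the true regression slope is. This has two consequences.

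- **Precision.** When r is well below 1, subtracting the whole baseline adds noise that a fitted slope would avoid.
- **Chance imbalance.** If the arms differ at baseline by chance, the change score subtracts the whole difference, although only the fraction r is expected to carry over to follow-up. The estimate is then shifted the other way by (1 − r) times the imbalance.

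The t tests between arms help with neither. Under sound randomisation their null hypothesis is true by construction, and their result enters no later step of the plan.

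At stake is power for outcomes of moderate stability in a trial of 60 women, and the closeness of the estimate to the truth in the one sample that is drawn.

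**Working it through.** **Inputs from the article.** 60 women, 30 per arm (Abstract); n = 23 for lean mass with SD 1.7 and power 0.8, and a "projected drop-out rate of 25" % (Sample size); alpha 0.05.

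**Assumptions.** n = 23 is per arm; alpha is two-sided; SDs are equal at baseline and follow-up; r is between 0.5 and 0.98, because the article gives no correlation.

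**The plan's own figure.** 23/0.75 = 30.7, so 31 per arm or 62 in all. The cruder 23 × 1.25 = 28.75 gives 29 per arm or 58. Both lie within two women of 60. In the other direction, 30 × 0.75 = 22.5, so 22 per arm is used below.

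**Step 1: variances.** With s² the outcome variance at one visit, per woman:
- change from baseline: 2(1 − r)s²
- baseline-adjusted: (1 − r²)s²
- ratio of adjusted to change: (1 + r)/2

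**Step 2: cost of estimating the slope.** With n per arm, the adjusted variance is inflated by about 1 + 1/(2n − 4). At n = 22 this is 1 + 1/40 = 1.025. One error degree of freedom is also lost (41 instead of 42).

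**Step 3: power.** The effect is set so that the change score has 80 % power at 22 per arm (two-sample noncentral t).

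| r | (1 + r)/2 | × 1.025 | Adjusted power |
|---|---|---|---|
| 0.5 | 0.75 | 0.769 | 89 % |
| 0.6 | 0.80 | 0.820 | 87 % |
| 0.7 | 0.85 | 0.871 | 85 % |
| 0.8 | 0.90 | 0.923 | 83 % |
| 0.9 | 0.95 | 0.974 | 81 % |
| 0.95 | 0.975 | 0.999 | 80 % |

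The variances break even where (1 + r)/2 × 1.025 = 1, that is at r = 2/1.025 − 1 = 0.951.

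**Step 4: lean mass.** The article does not say whether 1.7 is the SD of a change or of a single measurement. If it is an SD of change, then 1.7² = 2(1 − r)s², so r = 1 − 2.89/(2s²). For an assumed cross-sectional SD of 5 to 8 kg:
- s = 5: r = 1 − 2.89/50 = 0.942; net ratio 0.971 × 1.025 = 0.995; power 80.1 %
- s = 8: r = 1 − 2.89/128 = 0.977; net ratio 0.989 × 1.025 = 1.013; power 79.4 %

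So there is no gain for lean mass on that reading.

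**Step 5: imbalance.** With 30 per arm the chance baseline difference has SD √(2/30) = 0.26 outcome SDs. It exceeds 0.25 SD in 33 % of trials and 0.5 SD in 5 %. Given an imbalance D, the change contrast is shifted by −(1 − r)D:
- a one-SD imbalance (D = 0.26) at r = 0.6: 0.4 × 0.26 = 0.10 SD
- D = 0.5 SD at r = 0.5, 0.7, 0.9: 0.25, 0.15, 0.05 SD

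**Step 6: validity.** In a simulation without a treatment effect (23 per arm, compound symmetry, 3,000 runs per setting), the group-by-time test rejected in 4.9, 5.1 and 5.2 % of runs at r = 0.5, 0.7 and 0.9. The error rate is as planned.

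**The case against.** The strongest reply is that nothing is broken. Group-by-time ANOVA is a legitimate and common analysis, it keeps its type I error, and over repeated randomisation its estimate is unbiased. That stands in full.

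It can also be said that the gain depends on a correlation that the article does not give, and that the simple ratio (1 + r)/2 flatters adjustment in a small trial. Both are right. The 2.5 % inflation and the lost degree of freedom are therefore in the power figures. With them, adjustment is no better than the change score from about r = 0.95, and very slightly worse above it. Lean mass, the co-primary outcome with the larger stated n, may lie there. For VO2peak the article gives neither an SD nor a correlation, so its gain cannot be placed.

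A reader might infer that chance imbalance stays in the planned treatment comparison. The article does not support this for its stated target: the interaction compares changes, so the baseline difference is subtracted, and somewhat too much of it. An imbalance would carry through uncorrected only in a comparison of arm means at a follow-up visit, or averaged over visits, should the least-significant-difference step be used in that way.

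A reader might also infer that the baseline t tests will lead to adjustment for whatever turns out significant. The article plans no such step, and any figure for how often one test would be significant needs a count of independent tests that it does not give.

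Finally, an unseen analysis plan could add a covariate. But the article names the method for all variables, so this is a choice it makes and not a detail it leaves open.

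**Conclusion.** The point holds as one of efficiency and of error conditional on the observed baseline, not of validity. The planned analysis uses baseline less well than it could. For outcomes with r of about 0.5 to 0.8, adjustment would lift 80 % power to about 89 to 83 %. At r = 0.9 the gain is about one percentage point, and from about 0.95 there is none. The planned contrast also over-corrects a chance imbalance by (1 − r) times its size, typically about 0.10 SD at r = 0.6.

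These sizes rest on assumed correlations, equal SDs, two-sided alpha and 22 women per arm. They compare one follow-up-versus-baseline contrast with its adjusted counterpart, not the whole three-degree-of-freedom interaction test. Claims that the planned test is biased, that its error rate is inflated, or that every outcome would gain go beyond what the article supports.

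**What to change.** Replace the efficacy sentence in the Statistical analysis section by a model with the 3-, 6- and 12-month values as responses, group by visit as the effect of interest, and the woman's own baseline value, by visit, as covariate. The longitudinal model that keeps baseline among the responses but constrains the arm means there to be equal is an alternative. Report the adjusted EXER minus ER difference with its 95 % CI. Describe baseline by arm, and drop the significance tests there.

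The cost is one paragraph of wording, one or a few degrees of freedom, and a negligible change in precision for very stable outcomes. No visit, measurement or participant is added. The Trial status section reports recruitment as ongoing, so the change can still be made before the data are analysed.

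### The missing-data sentence merges EM replacement with multiple imputation and feeds an ANOVA written for one completed table; if a single EM fill is used, either type I error rises or the effect shrinks

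*Protocol article*

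**What the plan says.** All of this is in the protocol article.

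- Missing data (Statistical analysis): "Missing values for variables will be replaced using an expectation maximisation algorithm with a multiple imputations method", in Genstat.
- Main test (same section): a repeated-measures ANOVA, "mixed between-within subjects or split-plot) with intention-to-treat protocol for all variables to assess the interaction effect (group × time) will be performed".
- Follow-up comparisons (same section): "Analysis for the least significant difference of the means will be performed for both time and group", with the p "value set at 0.05".
- Visits (Measures): "Outcome measures will be obtained from participants at baseline, 3, 6, and 12 months".
- Expected loss (Sample size): 60 women, based on earlier evidence "plus a projected drop-out rate of 25" per cent. The Abstract gives 30 women per arm.

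The section does not say that a single completed table is analysed. Nor does it describe separate analyses that are then combined.

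**The concern.** EM and multiple imputation can be used together, but as ways of filling gaps they are not interchangeable. EM fill puts a conditional mean in each gap and yields one table. Multiple imputation draws each gap several times at random, analyses each table, and adds the between-table variance to the standard error. The sentence names both and so does not fix one procedure.

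The surrounding text leans towards one table. Values are replaced, and what follows is an interaction F-test and LSDs, each computed from one set of means and one residual mean square. Rubin's rules for a single estimate do not carry over directly to an F-test with several degrees of freedom or to LSDs. Even on the multiple-imputation reading, then, the named tests and the named missing-data method do not join up as written.

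About a quarter of the 12-month values of the two co-primary outcomes would be filled in. If those count as measurements, error bars are too narrow (fill uses arm) or the arms are pulled together (fill ignores arm).

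**Working it through.** **Inputs from the article.** 30 per arm; four visits; 25% drop-out; alpha 0.05 (taken as two-sided); n = 23 for lean mass, read as per arm.

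**The plan's own figure.** 23 / (1 − 0.25) = 30.7, so 31 per arm or 62 in total. The stated 60 is within two women of this. With 60 recruited, 0.75 × 30 = 22.5 women per arm reach month 12, against the 23 required. There is no slack, so the handling of the missing quarter matters.

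**Hand check 1: fill within arm.** Suppose 8 of 30 per arm (7.5 rounded up) leave straight after baseline and each missing change gets the arm's mean. This ignores what baseline predicts, so it is the extreme case.

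- Filled values add nothing to the sum of squares, but degrees of freedom rise from 42 (2 × 21) to 58 (2 × 29), and n per arm from 22 to 30.
- Reported SE / correct SE = √(42/58 × 22/30) = √0.531 = 0.73.
- The test rejects when |t| exceeds 2.00 × 0.73 = 1.46 on a statistic that truly has 42 degrees of freedom. That probability is about 15%.

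This is the upper end for the 12-month change. Simulation with a proper EM fill gave mean SEs at 73–80% of the true value.

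**Hand check 2: fill ignoring arm.** In the same setting the 8 filled women per arm carry no treatment difference, so the expected estimate is 22/30 = 73% of the truth. If some drop-outs have later visits, those visits carry part of the effect and the loss is smaller. Simulation gave 74–89%.

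**Simulation under no effect.** Drop-out was completely random and monotone, at 25% in each arm. It was either staggered or all straight after baseline. Assumed visit correlations were compound symmetry 0.5, compound symmetry 0.8, and AR(1) 0.8. There were 1,500 trials per setting, and 250 per setting for multiple imputation (m = 10, bootstrap-EM). Ranges below run over these settings.

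| Handling | Group × time F-test | t-test, 12-month change |
|---|---|---|
| Complete data | 5–7% | 4–6% |
| Single EM fill, arm in model, staggered | 13–16% | 10–14% |
| Single EM fill, arm in model, early drop-out | 21–25% | 13–14% |
| Single random draw, arm in model | 12–21% | 9–13% |
| Single EM fill, arm left out | 5–8% | 4–5% |
| Multiple imputation, Rubin's rules, arm in model | not run | 3–7% |
| Multiple imputation, Rubin's rules, arm left out | not run | 1–2% |

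Other runs of the single EM fill with arm in the model gave 14–23% for the F-test and 10–15% for the 12-month change. The single-draw row shows that restoring residual scatter is not enough; the pooling step removes the inflation. The Monte Carlo standard error for multiple imputation is about 1.4 points.

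The LSD contrast at 12 months rejected in 11–15% under compound symmetry with the arm-specific fill. Under AR(1) it rejected in 19–23%, but already in 12–13% with complete data, so that excess is only partly due to the fill.

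**The case against.** The strongest reply is that the sentence names multiple imputation. EM can legitimately supply the parameters for it, and the pooled version run above did exactly that and held its error near 5%. A one-sentence summary in a journal article need not give the number of imputations, the imputation model or the pooling rule. Those may be in the full protocol or an analysis plan that is not shown.

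Most of this stands. A reader might infer that the trial has committed itself to single EM replacement and therefore to a type I error well above 5%. The text does not support that: it never says one table is analysed, and it names a method that, properly pooled, has no such inflation. Nor is the absence of imputation details a fault in itself.

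The inflation figures also rest on assumptions outside the article: a single fill, arm in the fill model, drop-out timing and visit correlations. With arm left out, there is essentially no inflation.

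What the reply does not remove is the mismatch in the stated text. Two different procedures share one sentence, and the tests that follow are written for one completed table. Whoever runs the analysis must depart from part of the wording, and the permitted readings give materially different results.

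**Conclusion.** The point holds as a conditional one, of moderate severity.

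- If one EM-completed table is analysed with arm in the fill, nominal 5% tests run at about 10–15% for the 12-month change and about 13–25% for group by time. The upper figures need all drop-out to fall straight after baseline.
- If arm is left out, error stays near nominal, but the estimated effect is about 74–89% of the truth.
- If several imputed data sets with arm in the model are analysed and pooled, error on the 12-month change is about 3–7% and there is no problem.

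These sizes assume 30 per arm, 25% drop-out completely at random and equal between arms, and the visit correlations listed above. The direction of each effect does not depend on the exact correlations.

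**What to change.** Choose one of two routes and say so.

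1. Drop the EM replacement. Analyse all observed values of all randomised women with a REML mixed model for repeated measures (group, time, group by time), and report the 12-month group contrast from it. Women with partial follow-up stay in, under missing at random.
2. Keep imputation, but state that it is multiple imputation carried out by arm, using baseline and earlier visits. Analyse each data set separately and pool the 12-month group contrast by Rubin's rules.

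Under either route, do not run the ANOVA or LSDs on one EM-completed table.

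The cost is a change of wording and modest changes to code; no design or data-collection element is touched. The Trial status section reports recruitment still under way, so at that stage the change could precede analysis. Confidence intervals will be slightly wider than from a single filled table, which is correct.
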